## Background and rationale

Ghana has made considerable progress on key human capital indicators, such as reducing infant and child mortality rates, and has seen a significant rise in institutional deliveries over the past decade [1]. However, many hospitals still face shortages of critical resources needed to treat high-risk patients, while the growing workload negatively impacts the quality of care provided [2].

Ghana’s maternal mortality was 263 per 100,000 live births in 2020 [3] and neonatal mortality rate 22.8 per 1,000 live births, both remaining behind targets set by the United Nations Sustainable Development Goals [4].

The need to build the capacity of healthcare providers is widely acknowledged. Given the common challenges of low adherence to best practices and the limited fiscal space in government budgets, officials are emphasizing the need to better utilize existing resources. Peer-to-peer learning, supervision, and support—through feedback and mentoring—are seen as essential for maintaining quality.

The Obstetric Triage Implementation Package (OTIP) is designed to address these needs. OTIP consists of a 1-week on-site training on clinical knowledge to quickly assess and prioritize the care of pregnant women, with the goal of promptly and accurately identifying the severity of a patient’s condition, determine the appropriate level of care, and ensure that those with the most critical needs receive immediate attention.

A key innovation of OTIP is the designation of up to ten midwives per hospital as ‘Champions’—those selected to attend onsite training and lead the implementation of the new triage protocol. These Champions are responsible for training their peers, as well as monitoring and motivating the adoption of the protocol among colleagues and setting up and maintaining a triage room.

Pilot studies have demonstrated significant reductions in patient waiting times, highlighting the potential to improve both the efficiency and quality of service delivery [5, 6], consistent with evidence from on-the-job training by more experienced or skilled workers in the education sector [7, 8]. However, the scalability of OTIP and its effectiveness remain uncertain. Conducting rigorous research on its implementation at scale is critical, as promising interventions often face challenges in scaling up [9].

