### Objectives

The project’s key research questions are as follows:What is the impact of OTIP on the quality of service during labor and delivery, as well as on maternal and neonatal survival, and on neonatal health outcomes? To what extent does OTIP affect clinical knowledge and midwives’ attitudes? 

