### Methods and trial design

This study uses a cluster randomized controlled trial (cRCT) to evaluate the impacts of the introduction of the OTIP Champions program across high-volume hospitals in the final phase of its nation-wide rollout. The cRCT will be integrated into the final phase of the national rollout of the OTIP training program, covering the Central, Greater Accra and Western regions. 12 of the 25 hospitals are randomly assigned to receive OTIP training in September 2024, and the remaining 13 receive OTIP approximately 4 months later. Figure 1 is the design flow diagram. SPIRIT reporting guideline were used [11].

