#### Outcomes

We consider two sets of primary outcomes:Process variables: Representing the actual medical care received by mothers and their new-borns (e.g., time until initial assessment; assessment received upon arrival; doctor intervened if complications during labour and delivery at the hospital; postnatal checks).Maternal and neonatal outcome variables: Including the health of pregnant women and new-borns (e.g. maternal and neonatal mortality; complications during labour and delivery at the hospital; APGAR scores).

To examine mechanisms behind potential impacts of OTIP on the primary outcomes, we further consider secondary outcomes:Hospital staff outcomes: Such as improved knowledge and midwives’ attitudes capturing their perceptions of autonomy, empowerment and motivation.

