#### Participant timeline

Hospitals were randomized into early and late treated in July 2024. Pre-intervention implementation data was collected in September 2024. The first set of OTIP trainings took place in October 2024, the second will be conducted in February 2025. Data collection for primary outcome analysis will be conducted in January 2025. Mothers for the impact analysis will be recruited from early January 2025 and data collection is expected to take one month. The participant timeline is presented in Fig. 3.

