#### Sample size, sampling, and recruitment

The total targeted sample size for the cRCT will be in-person interviews with 750 staff, and 1,250 patients (mothers) per data collection round. In addition to the in-person survey we will administer online surveys to all the midwives on permanent contracts working in each hospital to collect data on clinical knowledge (1,338 midwives in total).

The patients target sample sizes proportional to each hospital’s delivery caseload in August-October 2023. This results in a minimum sample size of 35 and a maximum sample size of 65 per hospital. The inclusion criteria will be those who delivered in the hospital within the last two months, primarily from labor wards, postnatal wards, and postnatal care clinics. This eligibility criteria implies that in each survey round, we will interview a new cross section of 1,250 mothers. For mothers 18 years or younger, interviews will only be conducted if a guardian is present and provides consent in addition to the mother doing so herself. Mothers will only be approached for interview if not in distress due to, for example, having lost their child during labor. We will cross-check with hospital staff whether mothers can be approached or not.

The sample of midwives for these interviews will consist of the 10 midwives nominated by management or their peers to become champions (of whom 7 will ultimately be selected for training) and a random sample of 20 other midwives with permanent contracts in the maternity department, resulting in a total midwife sample of 750 midwives. We will not interview any students or staff on temporary contracts in the hospital. We aim to interview the same set of midwives throughout the study.

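### One third of the late-arm staff sample are already Champion nominees, so the pooled attitude contrast may not measure OTIP against no OTIP

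*Protocol article*

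**What the plan says.** **Question and outcome.** The Objectives section of the protocol article asks "To what extent does OTIP affect clinical knowledge and midwives’ attitudes". The Outcomes section lists, as secondary outcomes meant to explain mechanisms, knowledge and "midwives’ attitudes capturing their perceptions of autonomy, empowerment and motivation".

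**Champions as part of OTIP.** Background and rationale introduces the title of Champion with the words "A key innovation of OTIP is the designation of up to ten midwives per hospital as". The Intervention section also describes how Champions are selected, by management or by fellow midwives, on leadership and teaching ability.

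**Staff sample.** Under Sample size, sampling, and recruitment: "The sample of midwives for these interviews will consist of the 10 midwives nominated by management or their peers to become champions". Seven of these ten are later chosen to be trained. Another 20 permanent midwives per hospital are drawn at random, which brings the total to 750. On follow-up, that section states: "We aim to interview the same set of midwives throughout the study".

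**Timing.** Methods and trial design states: "12 of the 25 hospitals are randomly assigned to receive OTIP training in September 2024, and the remaining 13 receive OTIP approximately 4 months later". Participant timeline states: "Pre-intervention implementation data was collected in September 2024". It places early training in October 2024, outcome data collection in January 2025 and late training in February 2025. The two sections differ on the month of early training, but both put it before January 2025.

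**Analysis.** Statistical methods codes exposure as allocation to early OTIP and applies the same design to staff outcomes. It does not distinguish nominees from other midwives.

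**The concern.** In a delayed-start trial the late arm stands in for the absence of the programme. For attitudes such as empowerment and motivation, being put forward by managers or peers for a leading role could itself have an effect. The protocol presents Champion designation as a feature of OTIP, yet its first step, nomination, has been taken in both arms by the time outcomes are measured.

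For nominees, the early-versus-late contrast then answers a narrower question than the stated objective: what training and roll-out add once a midwife has been nominated. For the other 20 midwives per hospital it remains closer to OTIP against no OTIP. A single pooled coefficient mixes the two. The practical risk lies in interpretation, because a small or null pooled result could be read as evidence that OTIP does not work through attitudes.

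**Working it through.** **1. Are there nominees in the late hospitals?** 25 × (10 + 20) = 750, which is the stated total. It cannot be reached unless every hospital, early or late, contributes 10 nominees.

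- Late arm: 13 × 10 = 130 nominees among 13 × 30 = 390 interviewees, 33.3%.
- Early arm: 12 × 10 = 120 among 12 × 30 = 360, also 33.3%.

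**2. Were they named before the outcome survey?** The same midwives are meant to be interviewed in each round, and the first round was in September 2024. The Interim analyses section also puts the characteristics of selected champions in the baseline report. So nominees were very probably identified by September 2024, and in any case in time to be sampled for January 2025. Late training follows in February 2025. This assumes that the staff follow-up belongs to the January 2025 round.

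**3. The plan's own precision.** MDE = k × SE, with SE = √{[1 + (m − 1) × ICC] × (1/n₁ + 1/n₂)}, SD = 1, m = 30, n₁ = 360, n₂ = 390 and k = 1.960 + 0.842 = 2.802.

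- ICC 0.01: SE = √(1.29 × 0.005342) = 0.0830; MDE 0.233 (Table 1: 0.236).
- ICC 0.1: SE = √(3.90 × 0.005342) = 0.1443; MDE 0.404 (Table 1: 0.410).

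Both agree with Table 1 within 1.5%. With 375 per arm and a multiplier of 2.84, both table values are recovered (0.236 and 0.410).

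**4. What the pooled contrast estimates.** Let D₁ and D₂ be the effects of full OTIP against no OTIP for nominees and non-nominees, and let a be the effect of nomination alone on a late-arm nominee. Assume that nomination in late hospitals leaves non-nominees unchanged. Then:

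- nominees: D₁ − a
- non-nominees: D₂
- pooled: (1/3)(D₁ − a) + (2/3)D₂ = D − a/3, where D = D₁/3 + 2D₂/3.

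**5. Size.** The protocol gives no value for a, so the values below are assumptions spanning both signs. D is set at the Table 1 MDE. Power is Φ[(D − a/3)/SE − 1.96], with the SEs of step 3.

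| a (SD) | D = 0.236, ICC 0.01: contrast | power | D = 0.410, ICC 0.1: contrast | power |
|---|---|---|---|---|
| −0.2 | 0.303 | 95% | 0.477 | 91% |
| 0 | 0.236 | 81% | 0.410 | 81% |
| 0.1 | 0.203 | 69% | 0.377 | 74% |
| 0.2 | 0.169 | 53% | 0.343 | 66% |

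**6. Precision of separate contrasts.** Same formula, 12 against 13 hospitals, k = 2.802:

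| Group | m | MDE, ICC 0.01 | MDE, ICC 0.1 |
|---|---|---|---|
| All staff | 30 | 0.233 | 0.404 |
| Non-nominees | 20 | 0.274 | 0.427 |
| Nominees | 10 | 0.370 | 0.489 |

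With the 2.84 multiplier and equal arms, the ICC 0.1 column reads 0.410, 0.433 and 0.495.

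**The case against.** **Nomination is not receipt of OTIP.** This stands. The protocol separates the 10 nominees from the 7 eventually selected for training, and Champions are defined by attending training and leading implementation. Nothing shows that late hospitals had training, the triage protocol, a triage area or Champion duties before February 2025.

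**The direction of any bias is not established.** This also stands. A reader might infer that effects on attitudes are understated. That requires late-arm nominees to have known of their nomination and to have responded positively; the protocol states neither. Disappointment at waiting would push the other way, and if nominees were not told, a is probably close to zero.

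**Naming nominees in both arms is a strength.** Correct. It gives comparable nominee strata, whereas sampling nominees only in early hospitals would bring in selection bias. If nomination preceded the baseline survey, that applies equally to both arms and creates no imbalance.

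**The protocol openly declares an early-versus-late contrast, and subgroup reporting can be left to an analysis plan.** Partly right. The contrast is declared, and the protocol cannot be faulted for not saying when nominees were told. But the Objectives ask about the effect of OTIP on attitudes, and the stated model is applied to all staff as one group. How that coefficient may be interpreted remains a fair point.

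**Non-nominees are not a perfectly clean group either.** True: where fellow midwives do the nominating, they have taken part. This is a reason not to rest the headline on non-nominees alone.

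**Conclusion.** The point holds as a question of what the staff contrast estimates, not as a demonstrated bias. Nominees make up one third of the late-arm staff sample and were identified before the outcome survey. If nomination alone changes attitudes by a, the pooled contrast departs from OTIP against no OTIP by a/3: 0.03 SD for an assumed |a| of 0.1 and 0.07 SD for 0.2, in either direction, and nothing if a is zero. Against the Table 1 MDEs, 0.07 SD is about 28% of 0.236 SD and 16% of 0.410 SD.

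This rests on late-arm nominees knowing of their nomination, on no effect of nomination on late-arm non-nominees, and on values of a that are not in the protocol. The early-versus-late comparison remains a valid randomised one. Only the secondary attitude outcomes are concerned; nothing in the protocol suggests that the primary process, maternal or neonatal outcomes are affected.

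**What to change.** In Statistical methods, where the design is extended to hospital staff outcomes:

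- keep the pooled staff estimate;
- also report the early-versus-late contrast separately for the 10 nominees and for the 20 randomly sampled non-nominees per hospital;
- label the nominee contrast as the effect of training and roll-out given nomination;
- state that a null pooled result will not be read as absence of an attitude mechanism.

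**Cost.** No data beyond those already planned are needed. Each stratum is less precise. At ICC 0.1 the non-nominee MDE is about 0.43 SD against 0.41 SD pooled, and the nominee MDE is about 0.49 to 0.50 SD. At ICC 0.01 the loss is larger, about 0.27 and 0.37 SD against 0.23 SD. The non-nominee contrast does not describe Champions, which is why it should accompany the pooled estimate and not replace it.

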#### Assignment of interventions

Randomization was conducted using Stata version 16 by researchers at the IFS. The randomization determined whether a hospital would receive the intervention earlier or later. The decision whether a patient is assigned to the intervention or control group therefore depends on the timing of inclusion. By end February 2025 all hospitals will have received the intervention and hence by then every patient will be included in treatment. There is no blinding. Inclusion in the study for assessment of intervention effectiveness will be completed by the end of January 2025.

#### Data collection and management

We will rely on two main sources of data. For the cRCT, we will mainly rely on primary collected data from patients (mothers), and from midwives through in-person interviews. To promote data quality, all enumerators attend a week-long training session before data collection. This includes classroom-based training as well as training in hospital settings. It also covers how informed consent should be obtained, implying that informed consent will be acquired by well-trained and vetted data collection staff before the commencement of any data collection. Lead enumerators were also involved in two weeks of extensive piloting of the survey instruments.

For the regression discontinuity design, we will utilize the District Health Information Management System II (DIMS II), an electronic platform managed by GHS to collect, record, and analyze health service data nationwide. We will use key indicators such as deliveries and mortality for mother and new-born pairs at the hospital and monthly level from before, during and after OTIP implementation.

Administrative records and collected data will be recorded electronically using password-protected laptops. Once data collection is completed, all data will be promptly uploaded to an encrypted folder and/or deleted from the laptops. Access to the encrypted folder will be restricted to the research team, with participants’ identities anonymized in any reports derived from the research.

Once results are published, an anonymized version of the dataset will be released publicly without any personally identifying information.

The project is compliant with the Ghana Data Protection Act 2012 Act 846, and the UK Data Protection Act 1998.

For further details on data management: please refer to the project’s management registration: https://ifs.org.uk/sites/default/files/2024-11/Data-protection-V2.pdf. Data availability is outlined in online supplemental material S2.

#### Statistical methods

For our process variables, we will estimate the intent-to-treat effect of the program. Our design is a cluster randomized controlled trial stratified by region.

We estimate the impact of OTIP on process and maternal and neonatal outcomes by estimating the following specification for the outcome *Y* of mother or baby *i* in hospital *j* in region *r* at time *t*:2$$Y_{ij}=\beta\;OTIP_j+\delta\;X_{ij}+Y_r+\epsilon_{ij}$$.

Where $$\:OTI{P}_{j}$$ indicates if a hospital is allocated to receive OTIP early, $$\:{\varvec{X}}_{ij}$$ is a vector of controls for hospital characteristics selected by machine learning methods, and $$\:{\gamma\:}_{r}$$ are region fixed effects, as we stratified our randomisation by region to ensure balance in earlier and later treated hospitals in each region.

To increase statistical power, we will leverage the panel nature of our data and use baseline values of the outcomes in our analysis. For observations with values collected at baseline and follow-up, we can use an ANCOVA design. For observations without baseline values, we can use a difference-in-differences specification, exploiting variation across early- and later-treated hospitals, before and after the introduction of OTIP in early-treated.

To investigate mechanisms behind the observed impacts, we will use the same design with hospital staff outcomes to understand whether any impacts are driven by changes in staff outcomes due to OTIIP, such as midwives’ clinical knowledge and attitudes.

Moreover, for outcomes with low serial correlation, we will follow [15] and pool the multiple follow-up measurements to average out noise and increase power.

Due to the small number of clusters (25), we will present a wild-bootstrap p-value that is robust to small numbers of clusters [16]. We will additionally adjust for multiple hypothesis testing by family of outcome. Lastly, we will test for balance using baseline data for outcomes for hospital, midwives and patients’ characteristics. We will also test if attrition is uncorrelated to treatment allocation, and in case of non-random attrition on treatment status, we will estimate our main specification using inverse probability weighting.

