#### Sample size and power

The cRCT will focus on 25 OTIP hospitals. We aim to interview on average 30 hospital staff per hospital and 50 mother-newborn pairs. In total, the sample for the cRCT will be 750 staff, and 1250 mother/newborns per data collection round.

We calculate minimum detectable effects (MDEs) using the following formula [13]:1$$MDE\left(\frac{\left(t_{\alpha/2}+t_\beta\right)^2\sigma^2(mp\left(1-R_c^2\right)+\left(1-p\right)\left(1-R_p^2\right)}n\right)^\frac12$$

$$\:\alpha\:$$ denotes the significance level, $$\:\beta\:$$ power, $$\:\rho\:$$ unconditional ICC, $$\:t$$ is the critical values of the t-distribution, $$\:\sigma\:$$ is the standard deviation of the outcome,$$\:\:n$$ is midwives/mothers per arm, $$\:m$$ is midwives/mothers per cluster, $$\:{R}_{c}^{2}$$ is proportion of cluster level variance component explained by covariates and $$\:{R}_{p}^{2}$$ is the individual equivalent. One can interpret the effect of $$\:{R}_{c}^{2}$$ and $$\:{R}_{p}^{2}$$ as altering the “variance inflation factor” of the power calculation– when they equal zero the formula reduces to the standard cRCT one, applicable in our case.

To calculate the minimum detectable effects (MDEs), we assume a significance level ($$\:\alpha\:$$) of 0.05 and power ($$\:\beta\:$$) of 0.8 using two-sided tests.

To estimate intra-cluster correlations (ICCs) for the outcomes we measure, we reference the 2005 WHO Global Survey on Maternal and Perinatal Health [14], which presents ICCs that were obtained from 97,095 pregnancies and 98,072 births taking place in a representative sample of 120 hospitals in eight Latin American countries:Process variables: ICCs range from a minimum of 0.0003 to a maximum of 0.563, with a median of 0.067.Maternal outcome variables: Median ICC of 0.011 (interquartile range 0.007–0.037).Neonatal outcomes: Median ICC of 0.054 (interquartile range 0.013–0.075).

For hospital staff outcomes, we use data collected by colleagues on midwives in Nigeria to get an idea of hospital staff outcomes. The data provide indices that capture emotional exhaustion, accomplishment, and depersonalization (based on the Maslach Burnout Inventory).Hospital staff outcomes: ICCs of 0.07 for emotional exhaustion, 0.12 for accomplishment, and 0.07 for depersonalization.

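### Equation (2) indexes its controls by mother but defines them as hospital characteristics only; a short list of pre-arrival mother characteristics would add modest precision for low-ICC outcomes and some case-mix protection

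*Protocol article*

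**What the plan says.** The Statistical methods section of the protocol article models the outcome of mother or baby i in hospital j on the arm, region fixed effects and X_ij. The subscript lets X vary by mother, but the definition says it "is a vector of controls for hospital characteristics selected by machine learning methods". No mother-level covariate is named.

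The same section plans ANCOVA where an observation has a baseline value, and offers difference-in-differences where it does not. It will also "test for balance using baseline data for outcomes for hospital, midwives and" patient characteristics, so some mother characteristics are collected, at least at baseline.

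Under Sample size, sampling, and recruitment, "in each survey round, we will interview a new cross section of 1,250 mothers". No mother therefore has a baseline outcome of her own.

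The MDE formula under Sample size and power has separate R-squared terms for the hospital and individual levels. Of these the plan says that "when they equal zero the formula reduces to the standard cRCT one, applicable in our case". It therefore credits covariates at neither level through these terms.

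**The concern.** A hospital-level control can reduce only the between-hospital part of the error. If a large part lies between mothers, a model with hospital controls alone leaves that part untouched, although it has a mother-level index and the survey collects mother characteristics.

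Case mix is the second issue. According to Participant timeline, hospitals were randomised in July 2024 and the mothers in the impact analysis are recruited from January 2025. There is no blinding (Assignment of interventions). Mothers with post-birth complications are not selected (Eligibility criteria), and hospital staff advise on who may be approached (Sample size, sampling, and recruitment). The make-up of the analysed sample could therefore differ by arm. The stated balance test uses baseline data, which come from different women.

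**Working it through.** **Inputs from the protocol article.** Two-sided alpha 0.05, power 0.80, outcome SD 1. Cluster size: "We aim to interview on average 30 hospital staff per hospital and 50 mother-newborn pairs", so m = 50. Allocation is 12 early and 13 late hospitals (Methods and trial design), so n1 = 600 and n2 = 650 mothers. The assumed ICC is 0.01 for maternal and neonatal outcomes and 0.01 to 0.3 for process outcomes. Table 1 also shows 0.1 for the mother/child row.

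**Assumption, not in the document.** Individual-level R-squared (Rp) of mother characteristics: 0.05 to 0.20.

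**Reproducing Table 1 (both R-squared terms zero).** MDE = (1.960 + 0.842) × sqrt[(1/600 + 1/650) × (m·ICC + 1 − ICC)]. This gives 0.194, 0.385 and 0.629 at ICC 0.01, 0.1 and 0.3. The stated values are 0.196, 0.390 and 0.637, so agreement is within 1.3%. Using t with 23 degrees of freedom gives 0.202, 0.402 and 0.656; the percentage changes below are the same either way.

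**Where the error lies.** The variance factor is m·ICC (hospital part) plus 1 − ICC (mother part).

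| ICC | Hospital part | Mother part | Factor | Mother share |
|---|---|---|---|---|
| 0.01 | 0.50 | 0.99 | 1.49 | 66% |
| 0.1 | 5.00 | 0.90 | 5.90 | 15% |
| 0.3 | 15.00 | 0.70 | 15.70 | 4.5% |

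On cluster size the article adds: "This results in a minimum sample size of 35 and a maximum sample size of 65 per hospital". At ICC 0.01 the mother share is 74% for m = 35 and 60% for m = 65. With m = 50 the two parts are equal at ICC = 1/(m + 1) = 1/51 = 0.0196. At the source medians quoted in the article, the mother share is 64% for maternal outcomes (0.011), 26% for neonatal outcomes (0.054) and 22% for process outcomes (0.067).

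**Effect of covariates.** The factor becomes m·ICC·(1 − Rc) + (1 − ICC)·(1 − Rp), where Rc is the hospital-level R-squared. For example, at ICC 0.01 with Rp = 0.10 it is 0.50 + 0.99 × 0.90 = 1.391, and sqrt(1.391/1.49) = 0.966, a 3.4% smaller MDE. The last column sets Rp to zero and Rc to 0.30, also an assumption, for comparison.

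| ICC | No covariates | Rp 0.05 | Rp 0.10 | Rp 0.20 | Rc 0.30 |
|---|---|---|---|---|---|
| 0.01 | 0.194 | 0.190 (−1.7%) | 0.187 (−3.4%) | 0.180 (−6.9%) | 0.184 (−5.2%) |
| 0.1 | 0.385 | 0.384 (−0.4%) | 0.382 (−0.8%) | 0.379 (−1.5%) | 0.333 (−13.6%) |
| 0.3 | 0.629 | 0.628 (−0.1%) | 0.627 (−0.2%) | 0.626 (−0.4%) | 0.531 (−15.5%) |

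**What the other planned adjustments do for mothers.** With a fresh cross-section each round, a baseline outcome can enter only as a hospital-level value. Difference-in-differences removes stable hospital differences but does not reduce the between-mother part. Across two rounds of equal size it doubles that part, to 2 × 0.99 = 1.98 at ICC 0.01.

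**The case against.** The strongest reply is that the model does not rest on hospital characteristics alone. Region effects, baseline outcomes and difference-in-differences are also planned, and the last of these removes stable differences in hospital case mix. That stands. It does not reach the between-mother error, or a change in who is recruited after allocation.

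A second reply is that the subscript ij already allows individual covariates, and that the exact list belongs in the analysis plan. The list can wait, but the article has already defined X, and the definition conflicts with its index.

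Several stronger readings are tempting, and the document does not support them:

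- **Most of the error lies between mothers throughout.** This is true only below an ICC of about 0.02. The plan assumes up to 0.3 for process outcomes, which are a primary set, and the cited neonatal median of 0.054 is also above that point.
- **The gain is 12% of the MDE.** This needs covariates that explain 10% of the variance and themselves have an ICC of 0.05. The factor then falls from 1.49 to 50 × 0.005 + 0.895 = 1.145. Of that fall of 0.345, 0.25 (72%) is between hospitals, where hospital controls could reach it too. The article presents the assumed 0.01 as already reduced by baseline data, so this would probably count the same gain twice.
- **Chance imbalance biases the estimate.** Under randomisation it is part of the sampling variance already in the MDE. Only differential recruitment would be a separate problem.
- **Midwife outcomes have the same gap.** The plan aims to re-interview the same midwives, and ANCOVA on a midwife's own baseline is individual-level adjustment.

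**Conclusion.** The point holds in a limited form. As worded, X_ij contradicts its own index, and no planned adjustment uses mother-level information for mother and newborn outcomes. At ICC 0.01 about two thirds of the error variance is beyond the reach of hospital controls. At 0.1 and above that share is small, and hospital-level adjustment should remain the main tool.

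The expected gain is modest: about 2 to 7% of the MDE at ICC 0.01 and 0.4 to 1.5% at ICC 0.1. It rests on the assumed Rp of 0.05 to 0.20 and, for maternal and neonatal outcomes, on the plan's 0.01 being right. Case-mix protection is useful at any ICC but covers measured characteristics only. This is an inexpensive improvement to a primary analysis and does not make the planned estimate invalid.

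A reader might also infer that every suitable covariate is already in hand. The document mentions patient characteristics only for the baseline balance test. It neither lists the items nor says that they are asked again in January 2025.

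**What to change.** - Keep the hospital controls, region effects and baseline-outcome adjustment.
- Reword the definition of X_ij so that it also includes a short prespecified list of mother characteristics settled before arrival that OTIP cannot affect. Draw it from what the survey collects, for example age and parity if both are asked in both rounds.
- State that anything triage can change is excluded.
- Tabulate the listed characteristics by arm for the January 2025 mothers, alongside the baseline balance table.
- Leave midwife outcomes unchanged where ANCOVA on the midwife's own baseline is used.

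The cost is a sentence or two in the analysis section, one extra table and a few more model terms, which 1,250 mothers can support. No new data are needed if the items are asked in both rounds, which should be confirmed first.

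### Attrition in the midwife panel is corrected only if a 25-hospital test links it to allocation; that test is weak for moderate gaps and does not react when equal numbers but different kinds of midwives leave (minor, cheap to fix)

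*Protocol article*

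**What the plan says.** The *Statistical methods* section of the protocol article sets out two steps. The first is a test: "We will also test if attrition is uncorrelated to treatment allocation". The second depends on its result: "in case of non-random attrition on treatment status, we will estimate our main specification using inverse probability weighting". No other handling of attrition is stated.

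The *Sample size, sampling, and recruitment* section shows whom this concerns. For midwives, "We aim to interview the same set of midwives throughout the study". For mothers, "in each survey round, we will interview a new cross section of 1,250 mothers", so they have no panel to drop out of. The rule therefore applies to the staff outcomes (knowledge and attitudes), which the *Outcomes* section lists as secondary and uses to study mechanisms.

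The same *Statistical methods* section recognises the limits of the design when it comes to treatment effects: "Due to the small number of clusters (25), we will present a wild-bootstrap p-value". It does not carry that caution over to the attrition test. It also says that baseline values of the outcomes will be used, with ANCOVA possible where both rounds are available.

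**The concern.** A significance test is being used as a gate. The rule works only if a non-significant result means that attrition is harmless, and there are two reasons why it does not.

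- **Power.** The test compares two groups of about a dozen hospitals. A moderate difference in attrition can easily miss significance.
- **Target.** Bias depends on who leaves in each arm, not only on how many. If the same share leaves in both arms, but tired or less motivated midwives leave in one arm and an average mix leaves in the other, the stayers are no longer comparable and the rates show nothing.

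Arm-specific leaving is plausible here. When the January 2025 data are collected, champions in early hospitals already have to train colleagues and run the triage room. Nominees in late hospitals do not, nobody is blinded, and motivation and autonomy are among the outcomes. What is at stake is the mechanism analysis: an estimate based on stayers could be read as free of attrition bias because a weak test did not reject.

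**Working it through.** **Inputs from the protocol article.** There are 25 hospitals, allocated 12 to 13 (*Methods and trial design*: "12 of the 25 hospitals are randomly assigned to receive OTIP training in September 2024, and the remaining 13 receive OTIP approximately 4 months later"). About 30 midwives are interviewed per hospital, 750 in total (*Sample size and power*: "We aim to interview on average 30 hospital staff per hospital and 50 mother-newborn pairs"). Significance is 0.05, with power "of 0.8 using two-sided tests". Table 1 gives midwife-level MDEs of 0.236 SD at ICC 0.01 and 0.410 SD at ICC 0.1.

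**Assumptions, because the article gives no figure.** Attrition of 5% to 15%, an ICC of attrition between 0.01 and 0.10, and the strength of selection as stated in steps 3 to 5.

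**Step 1: reproduce Table 1.** MDE = (1.960 + 0.842) × √(2 × (1 + 29 × ICC)/375).
- ICC 0.01: 2.802 × √(2 × 1.29/375) = 0.232, against 0.236 stated.
- ICC 0.1: 2.802 × √(2 × 3.90/375) = 0.404, against 0.410 stated.

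Both agree to within 2%, so Table 1 can be used to judge the precision of a comparison in this panel.

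**Step 2: power of the attrition test, by two routes.**

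*Route A, from the stated MDEs, with 15% attrition.* The SD of the indicator is √(0.15 × 0.85) = 0.357. The gap needed for 80% power is 0.357 × 0.236 = 8.4 points, or 0.357 × 0.410 = 14.6 points. Power at gap d is Φ(2.802 × d/needed gap − 1.96).
- 5 points: Φ(−0.30) = 38% and Φ(−1.00) = 16%.
- 8 points: 76% and 33%.

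*Route B, two-sided cluster-level t-test at 5% with 23 df, 12 against 13 hospitals of 30, 10% attrition in the late arm.* SE = √{(1 + 29 × ICC) × [p1(1 − p1)/360 + p0(1 − p0)/390]}, with power from the noncentral t.

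| Attrition ICC | Power, 10% v 15% | Power, 10% v 20% | Gap for 80% power |
|---|---|---|---|
| 0.01 | 41% | 90% | 8.5 points |
| 0.05 | 24% | 65% | 12.2 points |
| 0.10 | 17% | 46% | 16.0 points |

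The routes agree: about 16% to 41% power for a 5-point gap, and about 8 to 16 points needed for 80% power.

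**Step 3: what a missed gap would cost.** If leavers score 0.5 SD below stayers in both arms, 10% against 15% attrition shifts the contrast by (0.15 − 0.10) × 0.5 = 0.025 SD.

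**Step 4: equal rates, different leavers.** The stayers' mean differs from the full group's mean by attrition × (stayer mean − leaver mean). With a 0.5 SD deficit in one arm and none in the other:
- 5% attrition: 0.05 × 0.5 = 0.025 SD, which is 6% (0.025/0.410) to 11% (0.025/0.236) of the stated MDEs.
- 15% attrition: 0.15 × 0.5 = 0.075 SD, which is 18% to 32% of the stated MDEs.

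A simulation of 4,000 trials per scenario, with no true effect and outcome ICC 0.07, let the log-odds of leaving change by 1 per SD of the outcome. That is stronger selection, an implied leaver–stayer gap of nearly 0.9 SD (0.088/0.10). Unadjusted bias was 0.09 SD (10% loss) and 0.17 SD (20% loss) with selection in one arm, and 0.18 and 0.34 SD with opposite selection in the two arms. The test of rates rejected in about 5% of trials throughout, which is its own error rate.

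**Step 5: what ANCOVA removes.** With baseline-to-follow-up correlations of 0.3, 0.5 and 0.7, the bias after ANCOVA was about zero when leaving depended only on the baseline score. When leaving depended on the follow-up score, with the same selection slopes and 10% or 20% loss, 0.05 to 0.32 SD remained.

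**The case against.** The strongest reply is that the exposure is narrow and may be small. The panel consists of permanent-contract midwives followed from September 2024 to January 2025, so few may be lost. Step 3 shows that a missed 5-point gap is worth little by itself. The test is not weak everywhere: it detects 10% against 20% with 90% power at ICC 0.01. ANCOVA already handles leaving that is driven by the baseline score. The 5% level and the reading of the test as one of rates alone are natural but not spelled out. Part of the knowledge outcome also comes from an online survey of all 1,338 permanent midwives, which these calculations do not cover.

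All of this stands, and it sets the severity. It does not rescue the gate: the case of equal rates with different leavers is not a matter of power, and ANCOVA covers it only if leaving follows the baseline score.

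A reader might also infer that the planned weights would be useless because they are built on treatment status and so constant within an arm. The article does not support that. Treatment status is named as the trigger; what goes into the weights is not stated, and a condensed article may leave that to the analysis plan.

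**Conclusion.** The conditional rule is a poor choice for the midwife panel. Under assumed attrition of 10% to 15% and an attrition ICC of 0.01 to 0.10, the gate misses a 5-point gap more often than not, and a test of rates does not respond to a difference in the kind of leaver. A non-significant result would leave the staff outcomes with no attrition correction beyond ANCOVA.

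It would go too far to say that the staff effects will be biased, or by how much. The article gives no attrition rate, and the 0.025 to 0.075 SD example rests on an assumed 0.5 SD deficit in one arm only. Nor are the trial's primary results in question, since mothers are sampled afresh each round. This is a cheap improvement of minor severity.

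**What to change.** In *Statistical methods*, remove the test as a trigger. For staff outcomes from the midwife panel, report in every case:

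1. A descriptive comparison of leavers and stayers by arm, with a joint test of the arm and arm-by-baseline terms.
2. Next to the ANCOVA estimate, an inverse-probability-weighted estimate, with weights from baseline outcome, champion-nominee status, other baseline midwife characteristics and region, each interacted with arm.
3. A simple sensitivity analysis for leaving that depends on unmeasured factors, for example by shifting the assumed mean of the leavers in one arm over a stated range. Weighting on measured variables cannot address this.

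Report trimming bounds only if attrition rates differ by arm, and state their monotonicity assumption. With equal rates they trim nothing and return the unadjusted result, which would be false reassurance in the case of most concern.

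The cost is a change of wording, modest code, and one or two extra estimates per staff outcome. Weighting and baseline balance checks on midwives are already planned, so little or no new data should be needed.
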